## Abstract

Central retinal artery occlusion (CRAO; retinal stroke or eye stroke) is an under-recognized, disabling form of acute ischemic stroke which causes severe visual loss in one eye. The classical risk factor for CRAO is ipsilateral carotid stenosis; however, nearly half of patients with CRAO do not have high-grade carotid stenosis, suggesting that other cardiovascular risk factors may exist for CRAO. Specifically, prior studies have suggested that cardioembolism, driven by underlying atrial fibrillation, may predispose patients to CRAO. We describe the design of an observational, population-based study in this protocol. We evaluate two specific objectives: 1) To determine if atrial fibrillation is an independent risk factor for CRAO after adjusting for medical and cardiovascular risk; 2) To determine if use of oral anticoagulation can modify the risk of CRAO for patients with atrial fibrillation. This protocol lays out our strategy for cohort definition, case and control definition, comorbidity ascertainment, and statistical methods.

## Introduction

### Significance/overall impact

Central retinal artery occlusion (CRAO; retinal stroke or eye stroke) is an under-recognized, disabling form of acute ischemic stroke which causes severe visual loss in one eye. Despite its formal recognition as a form of stroke by the American Heart Association/American Stroke Association (AHA/ASA), there are no guidelines in stroke medicine, cardiology, or neurology to inform its management [1]. In parallel, the National Heart, Lung, and Blood Institute has identified an unmet need to improve the identification of patients harboring atrial fibrillation (AF), many of whom remain undiagnosed. There are estimated to be approximately 700,000 such patients in the US [2]. CRAO represents an intriguing new dimension in the identification of patients harboring AF and therefore at risk of a future, lethal cardioembolic stroke. An AHA/ASA Scientific statement endorsed by 6 other professional organizations in the US recently called for urgent research on its mechanistic underpinnings [1]. Until this critical knowledge gap is filled, there may be a vulnerable population exposed to future cardioembolic stroke.

### Biological rationale

The prevailing paradigm is that CRAO arises because of ipsilateral stenotic carotid plaque [3] releasing predominantly calcium or cholesterol emboli. However, this observation is drawn from studies evaluating patients with branch retinal arterial occlusion (BRAO) where emboli may be visualized on funduscopic examination [4]. This may have falsely increased the perceived contribution of calcium/cholesterol emboli to CRAO as these emboli are less likely to autolyze when compared with fibrin-based emboli and are thus visible longer. Recently, we demonstrated that tissue plasminogen activator (tPA, a drug that breaks up fibrin-based clots) improved the rate of visual recovery in some patients with CRAO, providing evidence against the assertion that CRAO is caused exclusively by cholesterol or calcium emboli [5–7]. Furthermore, over 50% of people with CRAO do not have high-grade ipsilateral carotid stenosis [8] and 30% of people with CRAO do not have even mild ipsilateral carotid disease [9].

### Prior work addressing this question

There is a higher burden of AF in people with CRAO than in the general population. One prior insurance-based cohort study in Taiwan described a higher incidence of CRAO in patients with AF than in the general population [10]. This study adjusted for age, sex and year of presentation but did not adjust for vascular risk factors or medication exposures. Additionally, other studies have reported a higher prevalence of AF in patients with CRAO [11, 12] than in the general population which lends credence to the hypothesis that the two conditions are associated. However, CRAO (like cerebral stroke) is a surrogate marker for vascular risk [8] so studies that comprehensively address this confounding are needed. We performed a study using healthcare cost and utilization project (HCUP) data from New York, California, and Florida hospitalizations and emergency department visits found that there was an inverse relationship between AF and CRAO [13]. However, this study lacked access to outpatient and prescription drug information, which resulted in systematic under-ascertainment of both AF and CRAO. Furthermore, this study could not evaluate whether exposure to anticoagulation in patients with AF could prevent the development of CRAO. Therefore, a study using inpatient, outpatient, and pharmacy claims data would be essential to definitively determine whether cardioembolism is a potential causative etiology for CRAO, and whether anticoagulation can modify this risk factor. That only 50–60% of people meeting guideline criteria for anticoagulation for AF are actually treated with an anticoagulant creates an intriguing opportunity to leverage real-world data to conduct a quasi-randomized study to examine the interplay between anticoagulation and CRAO risk [14].

## Materials and methods

This study was deemed exempt by the Duke University Institutional Review Board, protocol number Pro00110768.

### Aims

Our aims are as follows:

Determine if prevalent AF is a risk factor for CRAO independent of other vascular risk factorsDetermine if anticoagulant usage modifies the risk of CRAO among patients with AF by means of a quasi-randomized study focused on patients with established AF

### Design and setting

Retrospective, observational, population-level cohort study of patients with atrial fibrillation and matched controls using administrative claims data among a 5% sample of fee-for-service Medicare beneficiaries in the United States from 2000–2020. This data source allows us to follow unique patients longitudinally for the duration of their fee-for-service enrollment, regardless of state of residence.

### Sample size calculation

Power/sample size calculations were made on the basis of an unadjusted Cox proportional hazards regression model. Within the primary analysis of aim 1, assuming a loss to follow-up of 20%, 570,000 subjects (285,000 with AF and 285,000 without) would have 90% power to detect a hazard ratio of 2, at an alpha of 0.05. This conservatively assumes an event rate of 22/100,000 per year in the exposed group (a rate of 45/100,000 is reported previously) [10] and an event rate of 11/100,000 per year in the unexposed group (a rate comparable to that reported previously) [15]. A query of the Medicare 5% sample between 2000 and 2015 reveals 818,940 unique patients with AF and 11,400 unique patients with a new diagnosis of CRAO. Power calculations were performed with the *powerSurvEpi* package (R v4.0.3).

### Inclusion and exclusion criteria (Aim 1)

The inclusion criterion is continuous fee-for-service Medicare enrollment for at least 12 months prior to AF diagnosis or matched index date (July 1 of inclusion year) for controls and continuous enrollment in fee-for-service (FFS) Medicare after AF diagnosis/index date for at least 12 months or until death if death occurred before 12 months of continuous enrollment.

Patients with prevalent AF will be identified as follows:ICD-9-CM code 427.31 or ICD-10-CM code I48 in 2 outpatient claims or 1 inpatient claim within 365 days, in any diagnosis position of the claim [16–18]. The index date will be the date of the first qualifying inpatient claim or second qualifying outpatient claim. Patients will be required to have 12 months of FFS claims without an AF diagnosis prior to the index AF claims based on inclusion criteria.

Exclusion criteria are:

patients with any claim for CRAO in the 12 months prior to AF diagnosis or index date for controls (July 1 of potential inclusion year).

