### Analytical cohort

An analytic cohort will be generated by applying the below inclusion and exclusion criteria as follows:

All patients meeting the criteria for AF in the study period and meeting other inclusion/exclusion criteria will be identified as cases, and the date of AF diagnosis will serve as case’s index date for calculation of covariates. All remaining beneficiaries will be considered potential controls; inclusion and exclusion criteria will be applied based on an index date of July 1 for each year in the study period; all beneficiaries meeting inclusion/exclusion criteria for each year will be included in the potential control pool. For all potential controls with multiple index dates/years of eligibility, the year they contribute will be selected randomly. A multivariable logistic regression analysis will be conducted using cases and potential controls to create propensity scores for AF status; the final control group will be selected using propensity score matching to the AF cases.

Survival time for patients will be defined as the number of months from the index date when criteria were met. Patients will be censored at death, at the end of fee-for-service enrollment, or at the end of data availability. When 85% of the cohort has died or been lost to follow-up, we will censor remaining patients at that point to avoid instability in estimates due to very small numbers of remaining participants.

Details of the cohort analysis will be reported using RECORD guidelines for analyses of routinely collected data, including use of a patient flow diagram [24].

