#### Regression modeling (aim 1)

a) The study index date will be the date of the first AF claim in the study and July 1 in the first year of inclusion in the analytic cohort for controls for the purposes of our survival analysis.b) We will describe cumulative incidence of CRAO over time with the overlap-weighted cumulative incidence function and presented graphically for patients with and without atrial fibrillation. Next, a weighted, unadjusted cause-specific hazard model will be fit with AF as the univariable predictor and CRAO as the event of interest, with patients censored at death, at end of data availability, or at end of fee-for-service Medicare enrollment.c) Then, a weighted cause-specific hazard model, clustered by state, and adjusting for age, sex, race, cardiovascular comorbidities will be fitted. Directly adjusted cumulative incidence curves for AF and control patients will be created with adjustment for all model covariates [28].d) We will test the proportional hazards assumption for all models.e) Our primary analytical model will be an overlap-weighted model with propensity scores derived from the adjustment covariates previously described as predictors for the presence of atrial fibrillation. We will report our results with sequential adjustment to produce the fully-adjusted, weighted model. We employ this sequential adjustment strategy to provide insight as to sources of measured confounding.f) We will evaluate **positive control endpoints**. Our positive control endpoints will be any ischemic stroke (defined by ICD-9-CM 434.0, 434.00, 434.10, 434.11, 434.9, 434.90, 434.91, 436/ ICD-10-CM I66.09, I66.19, I66.29, I66.9, I63.40, I63.50, I67.89 in the primary diagnosis position in a hospitalization or ED visit) [29]. We will utilize the same modeling strategy as used for the primary outcome.g) We will evaluate **negative control (falsification) endpoints**. Our negative control endpoint will be hospitalized/ED urinary tract infection (including renal abscess and pyelonephritis) (ICD-9-CM 590.1, 590.11 590.2, 590.8 or 599.0/ ICD-10-CM N15.1, N39.0, N10). We will utilize the same modeling strategy as used for the primary outcome [30].h) We will perform several sensitivity analyses for outcome ascertainment.

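### Aim 1 makes 12 months of fee-for-service enrollment after index an entry condition with death as the only exemption, so the cohort is selected on later events that the plan elsewhere treats as censoring

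*Protocol article*

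**What the plan says.** Under Inclusion and exclusion criteria (Aim 1), the protocol asks for "continuous fee-for-service Medicare enrollment for at least 12 months prior to AF diagnosis" (or before the matched index date for controls). It then adds a second condition that looks forward: "continuous enrollment in fee-for-service (FFS) Medicare after AF diagnosis/index date for at least 12 months or until death if death occurred before 12 months". Death is the only way to satisfy that condition with less than a year of enrollment.

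Under Analytical cohort, the follow-up rule reads: "Patients will be censored at death, at the end of fee-for-service enrollment, or at the end of data availability". Regression modeling (aim 1) repeats it for the cause-specific hazard model, "with patients censored at death, at end of data availability, or at end of fee-for-service Medicare enrollment".

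On calendar time, Design and setting describes a "5% sample of fee-for-service Medicare beneficiaries in the United States from 2000–2020". Analytical cohort takes AF cases from the whole study period. For controls, "inclusion and exclusion criteria will be applied based on an index date of July 1 for each year in the study period". No section stops entry 12 months before the data end.

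**The concern.** Eligibility at index should depend on what is known at index. Here it depends on what happens in the following year. A patient with a CRAO in month 3 who leaves FFS in month 8 is deleted along with the event; a patient with the same event who leaves in month 13 is kept. For an admitted patient, neither FFS exit nor end of data can act as a censoring event during the first 12 months.

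The death exemption makes the selection one-sided: early deaths stay and early living leavers go. At the end of the data window the effect is complete, since a survivor cannot show 12 months of enrollment that the data do not cover.

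At stake are events and person-time that the source does record, the make-up of the last entry year, and first-year mortality, which is the competing event in the planned cumulative incidence curves. The hazard ratio is at stake only under further conditions, set out below.

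**Working it through.** **Plan's own figure.** The plan gives no number for this rule. Its sample size of 570,000 is nearly reproduced by a two-sided Freedman-type formula with one year of follow-up (assumed) and no inflation for loss: events = (1.960 + 1.282)² × ((1+2)/(2−1))² = 94.6, and N = 2 × 94.6 / (0.00022 + 0.00011) ≈ 573,132. That figure does not depend on the eligibility rule and is not used further.

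**Inputs from the protocol.** 12-month look-back; 12-month post-index requirement with death exempt; data 2000–2020; control index July 1 of each year; AF entry throughout.

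**Assumptions.** Data end December 31, 2020, with no later enrollment records. Entry is uniform over 2001–2020. FFS exit and mortality rates are not given, so ranges are shown.

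**Step 1: calendar check.** A control indexed July 1, 2020 has at most 6 observable months. An AF case indexed after January 1, 2020 has fewer than 12. (January 2020 might pass if enrollment is counted in whole months.) Survivors therefore fail and decedents pass. With one-year mortality d and hazard h = −ln(1−d), the share admitted is 1 − d/h for AF cases spread over 2020 and 1 − √(1−d) for July 1 controls:

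| Assumed d | AF cases indexed 2020 | Controls indexed July 1, 2020 |
|---|---|---|
| 5% | 2.5% | 2.5% |
| 10% | 5.1% | 5.1% |
| 20% | 10.4% | 10.6% |
| 30% | 15.9% | 16.3% |

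Everyone admitted is a death. With censoring, 100% would be admitted.

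**Step 2: apparent first-year mortality.** Take 100 entrants, 95 before 2020 and 5 in 2020, with 15% mortality and 5% exit.
- Before 2020: deaths 95 × 0.15 = 14.25; retained 95 × 0.95 = 90.25; mortality 14.25/90.25 = 15.8%.
- In 2020: about 7.5% die before the data end, 5 × 0.075 = 0.375, all retained.
- Together: (14.25 + 0.375)/(90.25 + 0.375) = 14.625/90.625 = 16.1%.
- Decedents from 2020 are 0.375/90.625 = 0.4% of the retained cohort.

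This simple count treats death and exit as mutually exclusive. With independent exponential times, let h = −ln 0.85 = 0.1625 and l = −ln 0.95 = 0.0513. Then P(death first) = h/(h+l) × (1 − e^−(h+l)) = 0.1463 and P(neither) = 0.8075, so mortality among those kept is 0.1463/0.9538 = 15.3%. Adding 2020 (5% of entrants, of whom 1 − 0.15/0.1625 = 7.7% are admitted) gives (0.95 × 0.1463 + 0.05 × 0.077)/(0.95 × 0.9538 + 0.05 × 0.077) = 15.7%. Either way it is about 16%.

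**Step 3: hazard ratio.** If CRAO times are independent of exit and death times, whether a patient is retained carries no information about CRAO, and the rates should not shift. A simulation agrees. It used 4 million per group, a true ratio of 2, one-year mortality of 20% (AF) and 8% (controls), and event rates scaled up 50-fold for stable counts:

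| Annual FFS exit, AF / control | Patients removed, AF / control | Events lost, AF / control | Rate ratio, censoring | Rate ratio, plan's rule |
|---|---|---|---|---|
| 5% / 5% | 8.8% / 9.4% | 1.4% / 0.9% | 1.997 | 1.995 |
| 10% / 5% | 13.0% / 9.3% | 2.4% / 0.9% | 1.995 | 1.992 |

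The second row shows that exit differing by AF status does not by itself move the ratio. Bias needs FFS exit (or, through the exemption, death) to be related to CRAO risk. The simulation does not cover that case, and the protocol gives no data on it.

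**The case against.** The strongest reply is that this is an enrollment window followed by ordinary censoring from month 12 on: debatable but workable, and the death exemption at least avoids requiring 12-month survival. The effect on the primary estimate is close to nil under independent exit, and the 2020 decedents are about 0.4% of the cohort. For controls the 2020 share is smaller than 1 year in 20 suggests, because one eligible year is drawn at random and living controls with earlier eligible years still enter through those. All of this stands and limits the size of the point. It does not make the rule sound, because entry still depends on the future and recorded events are still dropped.

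A reader might infer more than the protocol supports:

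- **That a share of the 570,000 planned subjects is lost.** That figure is the number needed for analysis; ineligible people are screened out beforehand. The sample size section reports 818,940 AF patients by 2015 against 285,000 required.
- **That the assumed 20% loss to follow-up contradicts the rule.** That loss is not tied to the first year and can occur after month 12.
- **That the rule brings forward the 85% administrative cut-off.** The cut-off counts deaths plus losses. With 15% deaths and 5% exit, first-year attrition is about 20% under censoring and about 16% under the rule, so early attrition falls.
- **That unequal early exit, say 5% of AF and 8% of control patients with a CRAO, inflates the first-year ratio by 0.95/0.92 = 1.03.** This adjusts only the event counts. Whole patients are removed, so person-time falls too, and the factor arises only if exit after a CRAO differs from exit among other patients in the same group.

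**Conclusion.** The point holds as a design flaw of modest numerical size. On the text alone, the Aim 1 eligibility rule removes people for events in the first year that the follow-up rules say should censor them, and it exempts only deaths. Decedent-only entry in 2020 follows if the data end in December 2020 and no later enrollment records are used; the protocol does not state the end month.

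The demonstrable cost is discarded events and person-time, a last entry year made up of deaths, and apparent first-year mortality of about 16% in place of an assumed 15%. A material bias in the hazard ratio is not shown. It would require FFS exit, or death through the exemption, to be related to CRAO risk, which the protocol neither supports nor rules out.

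**What to change.** In the Aim 1 inclusion criteria, delete the 12-month enrollment requirement after index. Keep the 12-month look-back, start follow-up at index, and let the stated censoring at end of FFS enrollment or end of data apply from the first day. If a minimum potential follow-up is wanted, limit index dates to 2019 or earlier for everyone, whatever their vital status.

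Review the matching post-index enrollment clause in Inclusion and exclusion criteria (Aim 2) at the same time, together with that section's separate exclusion of patients who die within 12 months. Removing the enrollment clause alone would leave that second selection in place.

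The cost is about one sentence and no new data. Some patients will contribute less than 12 months, which the hazard model already handles. The timeline section has cohort creation starting when the protocol is submitted, so the cohort step may have to be rerun.

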#### Regression modeling (aim 2)

a) In keeping with target trial emulation methodology as described above, the index date for patients exposed to anticoagulation will be the date of the first anticoagulant prescription drug claim occurring after the diagnosis of AF. For potential controls, only patients with no exposure to anticoagulation throughout the study period would be eligible to avoid selecting controls who start an anticoagulant during the follow-up period. For controls, inclusion and exclusion criteria will be examined for each year after AF diagnosis, and the midpoint of one random year will be selected as the index date for each control patient.b) Similar to Aim 1, patients diagnosed with CRAO precedent to or concurrent to AF diagnosis will be excluded and these patients will be examined in an exploratory analysis.c) Our primary analysis will utilize propensity score overlap weighting methodology to approximate a randomized design where baseline hazard of CRAO of patients receiving anticoagulation vs. not receiving is comparable. We will incorporate the following variables to define the propensity score: age, time since first AF claim, sex, geography, race, Medicaid dual eligibility, vascular comorbidities and non-vascular comorbidities relevant to the likelihood that a patient will be treated with anticoagulation (to include all of the comorbidity variables included for Aim 1 propensity score, as well as history of gastrointestinal bleeding or peptic ulcer disease (using validated ICD-9-CM codes 531.x (gastric ulcer), 532.x (duodenal ulcer), and 578.x (gastrointestinal hemorrhage) and their ICD-10-CM counterparts K25.x, K26.x, and K92.2) and history of intracranial hemorrhage (any of ICD-10-CM I60, I61, S06.3, S06.4, S06.5, S06.6 and their ICD-9-CM counterparts 430.x, 431.x, 432.x)) [32–35].d) Our principal effect of interest is the hazard of CRAO among patients treated with any oral anticoagulant agent compared to those not treated. Given variable patient adherence to anticoagulation, we will take advantage of the strength of Part D data (which records pharmaceutical fills rather than prescriptions) and treat anticoagulation exposure as a time-varying covariate for patients exposed to anticoagulation.e) We will perform identical sensitivity analyses as described in Aim 1.f) Table shells for the results of Aim 2 are shown in Table 8.

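### In Aim 1 the claim that dates AF can itself be a stroke or urinary infection event, and the rules for CRAO at the index date conflict

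*Protocol article*

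**What the plan says.** All places are in the Protocol article.

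- **AF definition** (Inclusion and exclusion criteria, Aim 1): the code qualifies "in 2 outpatient claims or 1 inpatient claim within 365 days, in any diagnosis position of the claim". The same section adds "Patients will be required to have 12 months of FFS claims without an AF diagnosis prior to the index AF claims", so the qualifying episode is the first record of AF in that window.
- **AF index date** (same section): "The index date will be the date of the first qualifying inpatient claim or second qualifying outpatient claim". Regression modeling (aim 1), item a, instead uses the date of the first AF claim.
- **Control index date** (Analytical cohort): "inclusion and exclusion criteria will be applied based on an index date of July 1 for each year in the study period".
- **Start of follow-up** (Analytical cohort): survival time is counted from the index date, and no lag is stated.
- **Control endpoints** (Regression modeling, aim 1, items f and g): ischemic stroke is taken from the primary position of a hospitalization or ED claim, and UTI from hospital or ED claims. For each: "We will utilize the same modeling strategy as used for the primary outcome".
- **CRAO exclusion, Aim 1 criteria:** "patients with any claim for CRAO in the 12 months prior to AF diagnosis or index date for controls". It is the only exclusion listed there.
- **CRAO exclusion, Regression modeling (aim 2), item b:** "Similar to Aim 1, patients diagnosed with CRAO precedent to or concurrent to AF diagnosis will be excluded".

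**The concern.** Take a patient admitted with an ischemic stroke whose work-up finds AF. Stroke is the primary diagnosis and AF a secondary one. Under the written rules this one claim sets time zero for the AF arm and also meets the definition of the positive-control event. An admission for UTI with AF newly recorded does the same for the negative control. In these patients the event came first and led to the AF code. A control's July 1 is tied to no contact with care, so the control arm has no matching cluster of events at time zero.

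Both Aim 1 control endpoints are at stake. A raised stroke hazard ratio could partly reflect how AF was found. A raised UTI hazard ratio could be taken for residual confounding when it is a timing artefact. For the primary outcome, the risk depends on which of two conflicting exclusion rules is programmed.

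**Working it through.** **1. The plan's own figure, used here as a baseline.** The sample size section gives 285,000 per arm, rates of 22 and 11 per 100,000 per year, HR 2, 90% power and alpha 0.05. Freedman's formula, two-sided: (1.960 + 1.282)² × (3/1)² = 94.57 events. Over one year, N = 2 × 94.57 / 0.00033 = 573,132, within 0.5% of 570,000. This match applies no 20% loss; with loss as N/0.8 it would be 716,415. At 285,000 per arm the expected number is 285,000 × 0.00033 = 94.05 events, with power 0.898. The timing problem does not depend on this calculation. It supplies the control rate and the cost of the fix.

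**2. Size of the artefact.** Let s be the share of AF patients whose index claim is itself the event, F the mean follow-up in years, r₀ the control rate per year and θ the true ratio. Events per AF patient are θ·F·r₀ + s, and per control F·r₀. So

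apparent ratio = θ + s / (F·r₀).

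**3. Stroke and UTI.** The documents give neither s nor r₀ for these endpoints, so both are assumptions. With no true effect (θ = 1):

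| r₀ per year | s | F = 1 | F = 5 | F = 10 |
|---|---|---|---|---|
| 1% | 1% | 2.00 | 1.20 | 1.10 |
| 1% | 10% | 11.0 | 3.00 | 2.00 |
| 2% | 5% | 3.50 | 1.50 | 1.25 |
| 4% | 1% | 1.25 | 1.05 | 1.025 |
| 4% | 10% | 3.50 | 1.50 | 1.25 |

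Even 1.05 would be distinguishable from 1 at this sample size. At 4% per year over five years, controls have about 285,000 × 0.04 × 5 = 57,000 events and the AF arm 59,850. Then ln 1.05 / √(1/57,000 + 1/59,850) is about 8 standard errors (unweighted approximation).

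**4. CRAO, two rules side by side.** Under the Aim 2 modelling text, concurrent CRAO is excluded in Aim 1 as well. Then s = 0 and there is no artefact from the index claim. Under the Aim 1 criteria read literally, only earlier claims exclude, so a first CRAO claim on the index date or within the index admission stays in. For that literal reading only, with r₀ = 11/100,000 and θ = 1, expected events per arm are 31.35 (1 year), 94.05 (3 years) and 156.75 (5 years). If s = 1 per 10,000 (assumed), 285,000 × 0.0001 = 28.5 events are added:

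- 1 year: (31.35 + 28.5)/31.35 = 1.91
- 3 years: 1.30
- 5 years: 1.18

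At 0.5 and 2 per 10,000 the one-year ratio is 1.45 and 2.82. A false ratio of 2 would need about 31 such patients in 285,000 (1 in 9,091) over one year, or 157 (1 in 1,818) over five.

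**5. Two AF dates.** For AF identified from outpatient claims, the criteria use the second claim and the modelling section the first. A CRAO claim between the two is a reason for exclusion under one and a follow-up event under the other.

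**6. What the planned analysis would catch.** Matching and overlap weighting balance the listed covariates, and none of these represents being in hospital at time zero. The proportional hazards test might show an early excess, but no action is tied to it.

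**The case against.** The strongest objection concerns the primary outcome. A reader might infer that CRAOs which brought AF to light are counted as events caused by AF. The documents do not support that. The Aim 2 modelling text states that concurrent CRAO is excluded as in Aim 1, and CRAO followed by AF has its own secondary analysis. The criteria alone also remove patients whose CRAO claim is dated before the AF index claim. This stands: for CRAO what remains is conflicting wording and two AF dates, and the CRAO ratios above arise only under the literal reading.

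A reader might also infer that the validity check described under Limitations fails. Its worked example is the known effect of anticoagulation on stroke and intracranial hemorrhage, which belongs to Aim 2, where treated patients are indexed at the first anticoagulant fill. So the point is confined to the Aim 1 use of the control endpoints.

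It can further be said that a raised UTI ratio would still signal differential ascertainment, which is a use of a falsification endpoint. That is partly right. The signal would exist, but it would point to the wrong source, and a simple date rule removes this source.

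Last, the article does not say that day-zero stroke or UTI events count, and such detail may sit in a fuller plan. It does, however, fix the index date, the start of follow-up and the endpoint definitions. Followed as written, these let the index admission count.

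**Conclusion.** The point holds for the Aim 1 control endpoints. The stated rules allow the claim that dates AF to be the stroke or UTI event as well, in the AF arm only. The direction is upward for both endpoints. The size cannot be obtained from the documents: under the assumed ranges it runs from 1.25 to 11.0 over one year and from 1.05 to 3.0 over five, and it shrinks as follow-up lengthens. One year is the unfavourable end for data spanning 2000–2020.

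For CRAO the finding is a contradiction to be resolved, not a demonstrated bias. If the concurrent exclusion is applied, the index-claim artefact is nil. If the Aim 1 criteria are programmed literally, the primary hazard ratio is biased upward by an amount that depends on an unknown share. Because eligibility for the primary outcome and both control endpoints are touched, this should be settled before analysis.

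**What to change.** 1. Reconcile the Aim 1 criteria, item a of the Aim 1 modelling section and item b of the Aim 2 modelling section on one AF index date.
2. Add *or concurrent* to the CRAO exclusion in the Aim 1 criteria, defined as a claim on the index date or within the index admission and its transfers. Apply the same exclusion to the any-RAO analysis. Excluding the patient, rather than ignoring the one claim, is needed because later visits can repeat the code.
3. For ischemic stroke and UTI, do not count claims from the index episode. Start follow-up the day after the index claim or discharge, and start controls the day after July 1.
4. Optional: a sensitivity analysis that starts both arms 30 days after index.

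The cost is a date condition in the cohort program and the loss of a few true very early events. At the plan's rates over one year, dropping the index day takes expected CRAO events from 94.05 to 94.05 × 364/365 = 93.8, and power stays at 0.898. A 30-day lag leaves 94.05 × 335/365 = 86.3 events and power 0.872. Both power figures use Freedman's formula, two-sided, before any loss to follow-up.
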